**7.0 Measurements**

*7.1 Strength and aerobic fitness*

Muscle strength will be assessed using 1 repetition maximum (1RM) testing of the following exercises: leg extension, leg press, chest press, horizontal row, lat pulldown and shoulder press. A 1RM test measures the maximum amount of weight someone can lift for a single repetition, while maintaining good technique. Aerobic fitness (VO_2peak_) will be measured using a graded, maximal exercise test on a bicycle ergometer. Briefly, participants will wear a facemask and begin peddling at ~50-70 rpm at a low resistance. The resistance will gradually increase until participants are no longer able to maintain a cadence of 50 rpm or until they request to stop.

*7.2 Physical function*

The short physical performance battery (SPPB) tests, along with grip strength and a 6 min walk test, will be used to assess physical function. The SPPB tests include a repeated chair stand test (time it takes for participants to stand up from a chair 5 times), a balance test and 8 feet walk test. The scoring system for the SPPB is standardized and will allow us to compare our results to the literature.

*7.3 Body composition*

FM, FFM and bone mineral density will be measured using dual-energy x-ray absorptiometry (DXA), and muscle thickness of the quadriceps muscle will be determined using ultrasound. Waist circumference will be measured using a tape measure at the top of the iliac crest.

*7.4 Satellite cell response*

Muscle cross-sections will be mounted onto glass slides and histochemically analyzed for the following markers of satellite cell activity: Pax7, MyoD, myogenin, myostatin, IL-6, GDF11.

*7.5 Muscle protein synthesis*

We will determine myofibrillar and sarcoplasmic fractional synthetic rate (FSR) by measuring the incorporation of ^2^H labeled alanine into muscle proteins using the precursor-product method. Following consumption of a 150 mL dose of D_2_O, ^2^H will quickly equilibrate with total body water (precursor pool). ^2^H will also become incorporated into the amino acid alanine, which in turn will become incorporated in muscle proteins. Using saliva swabs to assess ^2^H in the precursor pool, and muscle biopsies to assess ^2^H in the product pool, we can measure FSR in various muscle subfractions. Muscle samples will be purified in our laboratory. Both muscle and saliva samples will be analyzed using gas chromatography pyrolysis isotope ratio mass spectrometry (GC-*pyrolysis*-IRMS) and cavity ring-down spectrometry, respectively.

*7.6 Glucose metabolism*

A 2 hour 75g OGTT will be used to assess aspects of glucose metabolism. Briefly, after an overnight fast (no food or drink except for water after midnight the night before) a catheter will be inserted into an antecubital vein and a fasting blood sample will be drawn (~16 mL). Participants will then consume a beverage that contains 75g glucose within 5 minutes. Blood (~8 mL) will be drawn at the following time-points: 15 min, 30 min, 45 min, 60 min, 90 min and 120 min. The total amount drawn will be ~64 mL. We will measure blood glucose and insulin concentrations at every time-point, as well as the area under the glucose and insulin curves.

Other variables will also be measured in the fasting blood sample:

- Lipids: total cholesterol (TC), low-density lipoprotein cholesterol (LDL-c) and high-density lipoprotein cholesterol (HDL-c), as well as triacylglycerol (TAG) concentrations.
- Markers of bone health: 25-hydroxyvitamin D (25[OH]D), parathyroid hormone (PTH), osteoprotegerin (OPG), receptor activator of nuclear factor kappa-B ligand (RANKL)
- Liver enzymes and proteins: alanine aminotransferase (ALT), aspartate aminotransferase (AST), gamma glutamyl transpeptidase (GGT), albumin and total protein
- Cystatin C (for the estimation of glomerular filtration rate [to assess renal function])

*7.7 Cognitive function and quality of life*

Cognitive performance will be evaluated using validated neuropsychological assessment tools and cognitive tests will be included to get a full range of cognitive function:

| **Area of Interest** | **Validated Assessment Tools** |
| --- | --- |
| Global cognitive ability | - Montreal Cognitive Assessment (MoCA)^10^ - National Adult Reading Test (NART)^11^ |
| Language | - Boston Naming Test (BNT)^12^ - Controlled Oral Word Association Test^13^ |
| Memory | - Face recognition memory paradigm^14,15^ - Hopkins Verbal Learning Test –Revised (HVLT-R)^16^ - Brief Visual Memory Test - Revised (BVMT-R)^17^ - Rey Complex Figure Test, Wechsler Memory Scale – Revised - Logical Memory subtest, Autobiographical Interview – Abbreviated Administration^18^ |
| Attention | - Wechsler Adult Intelligence Scale – 3^rd^ Edition (WAIS-III) Digit Span Subtest^19^ |
| Inhibitory control | - Erikson Flanker Task^20^ |
| Working memory | - Directed Forgetting Test^21^ |

We will evaluate quality of life with a series of questionnaires designed to explore sleep quality, stress levels, daily activities, geriatric depression and subjective memory.

*7.8 Renal function*

We will estimate GFR using serum cystatin C concentrations. This will be measured using the fasting blood samples collected during the OGTTs performed at pre, mid (week 7) and post-study (week 19) testing.

*7.9 Diet analysis and physical activity*

Participants will complete a 3-day food diary and PA log during each assessment week. They will record everything the eat and drink, as well as any exercise they engage in, for 2 week days and 1 weekend day. Additionally, participants will wear and accelerometer (mounted on an armband) for the same 3 days so that we may estimate daily energy expenditure. The 3-day food diary, PA log and accelerometer will allow us to approximate daily caloric intake and macronutrient distribution, as well as to determine whether their dietary and activity patterns have changed throughout the course of the study.

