**4.0 Population under study**

For this study, we will recruit 50 sedentary yet healthy men aged 70 years or older (n=25 per group). Participants will be considered sedentary if they have not participated in a structured resistance or aerobic training program in the past 6 months. In addition, participants will have a BMI in the normal or overweight range (18.5 – 30.0 kg/m^2^), will have been weight stable for the past 6 months, and will present with a normal resting blood pressure or stage I hypertension at screening (SBP < 140 – 159 mmHg; DBP < 90 – 99 mmHg).

The following exclusion criteria exist to ensure the safety of participants and that certain outcome measures are not confounded:

- Smoking
- Use of simvastatin or atorvastatin
- Use of non-steroidal anti-inflammatory drugs
- Injuries that prevent safe participation in an exercise program
- Prescription blood-thinners
- Diabetes or other metabolic disorders
- Cardiac or gastro-intestinal problems
- Infectious disease or cancer

*4.1 Screening*

A variety of questionnaires and physiological tests will be used to assess eligibility for the study:

Medical Screening Questionnaire and Physical Activity Readiness Questionnaire (PAR-Q): Members of the research team will help potential participants complete a health questionnaire, which will assess the potential participant’s age, physical activity levels, and any medications and medical conditions that the individual may have. We will also measure height and weight. Potential participants must answer ‘no’ to all questions on the PARQ.

OGTT: Potential participants will also undergo a 2 hour 75g OGTT to determine whether they are diabetic (fasting blood glucose > 7.0 mM; 2 hour blood glucose > 11.1 mM) or display impaired glucose tolerance (fasting blood glucose > 5.6 mM; 2 hour blood glucose > 7.8 mM). Details of the OGTT protocol are described below.

Blood pressure: Systolic and diastolic blood pressure must be within the range indicated above in order for an individual to participate in this study. Participants will quietly rest in the supine position for 5 min before measurements are made using an automatic blood pressure cuff. A total of 3 measurements will be made, and the average will be used to assess resting blood pressure.

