Exercise stress test: Participants must demonstrate normal cardiac function during a graded, maximal exercise stress test on a cycle ergometer using a 12-lead ECG. All exercise stress tests will be conducted at the 3U Cardiorespiratory Clinic at McMaster University Medical Centre, under the supervision of a trained technician.

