**5.0 Sample size**

A total of 50 old, active men will be recruited; participants will be separated into 2 groups of 25 and each group will receive either SUPP or PLB. Previous studies have shown that supplementation with creatine monohydrate during RE training in older adults can increase dynamic strength by approximately 1.75 – 3.25 kg more than RE training alone. Using this effect size and a standard deviation of 1.5 kg, n = 20 subjects are needed to detect a difference with α = 0.05 and β = 0.8 using a two-way ANOVA. To account for the possibility of increased variability in the sample set and allowing for a potential 20% dropout rate, a conservative number of 25 subjects per group was chosen.

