**6.0 Design**

The overall study design is depicted in Figure 1, below. Participants will be placed in either the SUPP or PLB group, depending on their strength, fat-free mass and body mass index.

[figure not shown]

**Figure 1**. Study schematic. D_2_O, deuterium oxide; 1RM, 1 repetition maximum; VO_2peak_, peak oxygen consumption; OGTT, oral glucose tolerance test; QOL, quality of life assessment, PA, physical activity

*6.1 Assessments*

Approximately 1 week prior to beginning the study, participants will receive a muscle biopsy from *vastus lateralis*, exercise and physical function testing, body composition analysis, an OGTT, and an executive function and quality of life assessment (see Figure 1). These tests will take place over the course of 3-5 days during the same week. During the week these assessments are taking place, participants will complete a 3-day food diary and physical activity log at home, as well as wear an accelerometer (mounted on an arm band) to estimate daily caloric intake, macronutrient distribution and energy expenditure. We will assess glomerular filtration rate (GFR), an estimate of kidney function, by examining cystatin C concentrations in blood samples collected during pre, mid and post-study testing periods.

These assessments will be repeated during week 7, and again upon completion of the study during week 19. Exercise tests (1RM and VO_2peak_) will be repeated at weeks 11 and 15 to ensure an adequate exercise stimulus is maintained during training. The assessments at week 7 and week 19 include serial muscle biopsies for the measurement of the acute satellite cell response to exercise. Details of the serial muscle biopsy protocol are described below. Participants will be asked to refrain from strenuous exercise, caffeine and alcohol for 48 hours prior to each assessment.

*6.2 Phase 1*

Phase 1 of the study is 6 weeks in duration and will be completed primarily at home. Participants will consume 2 study beverages per day – the first approximately 1 hour after breakfast, and the second before bed. Participants will be encouraged to maintain their normal diets and levels of physical activity. We will provide participants with all their study beverages at the beginning of the study.

*6.3 Phase 2*

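### Within-arm strength change from pre-study to week 7 can contain learning of the 1RM test, and section 9.0 lets it be read as the independent supplement effect of hypothesis 1

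*Protocol*

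**What the plan says.** **Who is tested.** Section 4.0 recruits sedentary men aged 70 or older: "Participants will be considered sedentary if they have not participated in a structured resistance or aerobic training program in the past 6 months". Section 5.0 reads differently: "A total of 50 old, active men will be recruited". The two need reconciling. This point rests on the eligibility definition in 4.0.

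**What is rehearsed.** The only maximal effort at screening is on a cycle: "Participants must demonstrate normal cardiac function during a graded, maximal exercise stress test on a cycle ergometer". No lifting is described there. Section 7.1 says "Muscle strength will be assessed using 1 repetition maximum (1RM) testing of the following exercises", lists six lifts and requires good technique. It mentions no familiarisation, repeat test or best-of rule.

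**When strength is measured.** Section 6.1 puts the first tests about a week before the study: "These tests will take place over the course of 3-5 days during the same week". Then: "These assessments will be repeated during week 7, and again upon completion of the study during week 19". 1RM is also repeated at weeks 11 and 15 to keep the training load adequate. Between the pre-study test and week 7 lies Phase 1 (6.2), six weeks of study beverages mainly at home. Training runs for 12 weeks in Phase 2 (6.3).

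**What strength is used for.** Section 6.0 places men in SUPP or PLB "depending on their strength, fat-free mass and body mass index". Strength is part of the primary objective (2.0), which concerns exercise-mediated change. It is also the only outcome behind the sample size (5.0). Hypothesis 1 (3.0) expects supplementation and training each to raise strength independently as well as together.

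**How it is analysed.** Section 9.0 plans a two-way ANOVA with group (between) and time (within), followed by Tukey's HSD when interactions are found. No section names the baseline visit for the strength comparison.

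**The concern.** Phase 1 is the only period with supplement and no training, so it is where the independent effect in hypothesis 1 would be looked for. It is also the interval between a man's first and second described 1RM. If men lift more the second time simply because they know the test, both arms rise from pre-study to week 7 with no supplement effect at all.

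The interaction condition in 9.0 looks like protection, because a gain shared by both arms creates no group-by-time interaction. But the test covers all visits together. A true SUPP advantage that arises only during training makes the interaction significant. The Tukey step then compares all the means, including pre-study against week 7 within SUPP. A learning gain found there could be reported as evidence that the supplement works without training. The risk is greatest when SUPP crosses the threshold and PLB, by chance, does not.

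**Working it through.** **The plan's own figure.** Inputs from 5.0: difference 1.75–3.25 kg, SD 1.5 kg, α = 0.05, power 0.8 (printed as β), 20 per group before dropout. With n = 2(1.96 + 0.84)² × SD²/Δ², at 1.75 kg: 2 × 7.85 × 2.25/3.0625 = 11.5, so 12 per arm (13 by t-test). The stated 20 does not follow from these inputs; 20 per arm gives 95% power at 1.75 kg. The dropout step is correct: 20/(1 − 0.20) = 25.

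**Assumptions for the Phase 1 check.** The protocol gives no learning gain, so mean m and between-man SD L are assumed. The rest: 20 completers per arm; three visits (pre-study, week 7, week 19); change SD 1.5 kg without learning; learning carried from week 7 onward, alike in both arms; a supplement effect of 1.75 kg at week 19 only; none in Phase 1. The analysis is the group-by-time ANOVA, then Tukey over the six arm-by-visit means.

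**Does the interaction condition protect Phase 1?** The interaction was significant in 93–97% of simulated trials, because the Phase 2 effect is real. Among those trials:

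| Assumed learning | Tukey declares a pre-study to week 7 rise in SUPP |
|---|---|
| none | 0.3% |
| mean 1 kg, L = 1 or 0 | 40% to 54% |
| mean 1.5 kg, L = 1 | 83% |

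With a mean of 1 kg, SUPP alone reaches significance in about 24%. By symmetry, PLB alone does so about as often.

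**Hand check at L = 0.** The error mean square is 1.5²/2 = 1.125, so the Tukey critical difference is about 4.14 × √(1.125/20) = 0.98 kg. The standard error of a within-arm mean change is 1.5/√20 = 0.335 kg. For m = 1 kg the chance of exceeding 0.98 kg is Φ((1 − 0.98)/0.335), about 52%, in line with the simulation. For m = 0.5 kg it is Φ((0.5 − 0.98)/0.335), about 8%. The result depends strongly on the assumed gain.

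**Without the interaction condition.** A paired t-test in one arm (n = 20, SD 1.5 kg) finds a rise in 30%, 81% and 99% of trials for m = 0.5, 1.0 and 1.5 kg. The pooled time effect is significant in 54%, 98% and 100%.

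**Between arms.** The test of the SUPP minus PLB difference in pre-study to week 7 change stays near 5% throughout, because a shared gain cancels.

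**Power, as a range only.** If 1.5 kg excludes learning, the change SD from the pre-study value is √(1.5² + L²). Power with 20 per arm, two-sided 0.05:

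| L (kg) | SD of change (kg) | Power at 1.75 kg | Power at 2.5 kg |
|---|---|---|---|
| 0 | 1.50 | 94.9% | 99.9% |
| 0.5 | 1.58 | 92.7% | 99.8% |
| 1.0 | 1.80 | 84.9% | 99.0% |
| 1.5 | 2.12 | 72.0% | 95.3% |
| 2.0 | 2.50 | 57.8% | 86.9% |

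Power at 1.75 kg reaches 80% when the SD is 1.925 kg, that is L = √(1.925² − 1.5²) = 1.2 kg. At 2.5 and 3.25 kg the limits are about 2.3 and 3.2 kg.

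**The case against.** The strongest reply is that the design already contains the control. PLB goes through Phase 1 too, learns the same test and shows the same rise, so a careful reader would not credit the supplement. That stands for the between-arm comparison. It does not stand for the within-arm Tukey contrast, which 9.0 permits and which can be significant in one arm only.

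A second reply is that a missing rehearsal is operational detail. A practice session might sit in a testing procedure, and Figure 1 is not available, although its legend lists no such visit. This is fair. The reading rule below is needed only if learning remains, but does no harm otherwise.

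A reader might also infer more than the documents support:

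- *That the primary strength baseline is contaminated.* No section makes the pre-study value that baseline. The primary objective concerns exercise-mediated change, and the sizing effect is supplement plus training against training alone. Week 7 is the natural pre-training value, and the pre-study test then acts as its rehearsal.
- *That the trial loses power.* This needs a between-man learning SD that the protocol does not give. The 1.5 kg may already include such noise, and 5.0 says that 25 per group also allows for extra variability.
- *That placement is biased.* Noise in one of three placement variables weakens balance; it does not by itself bias SUPP against PLB.
- *That a practice 1RM is required.* It would be an extra procedure in a 3–5 day week that already holds a biopsy, an OGTT and exercise tests, with no strenuous exercise for 48 hours before each assessment.

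**Conclusion.** The point holds as a matter of interpretation. The schedule makes pre-study to week 7 the interval in which test learning would appear, and the Tukey step in 9.0 does not shield that interval once Phase 2 produces an interaction. With an assumed mean learning gain of 1 kg and no Phase 1 effect, a spurious SUPP rise is declared in about 40–54% of trials with an interaction, and in SUPP but not PLB in about 24%. At 0.5 kg the first figure is about 8% (L = 0); at 1.5 kg it is about 83% (L = 1).

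These figures rest on the assumed gain, on reading 1.5 kg as the SD of change, on three visits in the ANOVA and on Tukey over all six means. A different set of visits or family of contrasts would change the size but not the mechanism. The between-arm comparison is sound at about 5%, provided that the arms are comparable. A general loss of power or a biased treatment comparison is not shown.

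**What to change.** Add two statements to section 9.0.

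1. Any strength effect of supplementation without training is judged only by the SUPP minus PLB difference in pre-study to week 7 change, never by change within one arm.
2. The exercise-mediated strength comparison takes the week 7 1RM, done before the first training session, as its baseline. The pre-study test then serves as rehearsal.

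The second statement has a consequence to accept knowingly: change from week 7 measures what the supplement adds during training, and leaves out any Phase 1 effect. That effect is covered by statement 1.

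The cost is wording only, with no visits, samples or men added. If the effect of learning on power is discussed, show it as a range over the assumed between-man SD. If a familiarisation 1RM already takes place before placement, say so in 7.1. If not, adding one is optional and would have to fit around the biopsy and the 48-hour rule in 6.1.

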**8.0 Risks**

The potential risks and discomforts associated with the exercise testing and training procedures are similar to those associated with any form of strenuous physical activity. These include fatigue, fainting, abnormal blood pressure, irregular heart rhythm, and in very rare instances, heart attack, stroke or death. Every effort will be made to minimize these potential risks by ensuring all participants receive an exercise stress test prior to beginning the study, by evaluating preliminary information related to the health and fitness levels of subjects (using the health questionnaire and PAR-Q), and by careful observations during testing and training. Should any acute injury occur or if further medical assistance becomes required, we shall ensure that the necessary care is provided to our volunteers.

There is a risk of infection, bruising and soreness any time the skin is breached, as with muscle biopsies and blood sampling. To minimize risk and discomfort to our participants, all biopsies will be performed by [name]., who has training and experience with this procedure. All blood draws will be conducted by trained members of the research team, and all equipment will be sterile. Participants will be instructed on the proper care of their biopsy blood draw sites.

The risk associated with DXA and D_2_O is minor. DXA involves the use of whole-body x-ray, however the dose of radiation is less than one would receive when taking a transatlantic flight. Nausea and vertigo have been reported as side-effects of D_2_O consumption. However, the dose used in this study is small and unlikely to cause any symptoms.

**9.0 Data analysis**

Data will be analyzed using a 2-way analysis of variance (ANOVA) with between (SUPP, PLB) and within (time) group comparisons. Tukey’s HSD post hoc testing will be used to assess differences between the means when interactions are detected. Statistical significance will be accepted at α<0.05.

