**2.0 Objectives**

This study will examine the effects of a 12 week RE + HIIT exercise training program combined with multi-ingredient protein-based supplementation (SUPP), compared to 12 weeks of training combined with placebo (PLB), in older men. The substantive objectives of this study are to determine:

1. Primarily, whether the supplement is able to enhance exercise-mediated changes in muscle strength, physical function and body composition.
2. The acute satellite cell response to a single bout of HIIT + RE following 12 wks of protein or placebo supplementation.
3. The effect of each intervention on:
   1. Glucose metabolism and fasting serum lipids.
   2. Cognitive and executive function
   3. Renal function.

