**3.0 Hypotheses**

1. Supplementation and exercise training will independently and synergistically increase muscle strength and physical function, as well as augment fat-free mass (FFM) and reduce fat mass (FM).
2. The acute satellite cell response will be greater/less impaired after 12 weeks of protein supplementation compared with placebo.
3. Myofibrillar and sarcoplasmic MPS, glycemic control, lipid partitioning, executive function and quality of life will improve in response to supplementation + exercise and exercise alone, and to a lesser extent following supplementation alone. Neither supplementation nor placebo training will alter renal function.

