During Phase 2, participants will perform 3 exercise sessions per week for 12 weeks, while continuing to consume 2 study beverages per day. On non-exercise days, they will consume their beverages exactly as they did in Phase 1: the first 1 hour after breakfast and the second before bed. However on days when they visit McMaster University to exercise, participants’ first study drink of the day will be provided to them upon completion of the exercise session. The second study drink will be taken before bed, as usual.

*6.4 Exercise training*

Exercise training will take place three times per week for 12 weeks. One session per week will consist of HIIT on a bicycle ergometer, and 2 sessions per week will consist of whole body RE. Before beginning a HIIT session, participants will warm up on the bicycle ergometer for 5 min at a low resistance. The exercise will consist of 10 bouts of 60s where participants will sprint (ie. maintain a cadence of at least 90 rpm) at a power predetermined to elicit 90% HR_max_. These bouts will be interspersed with 60s of ‘rest’, where participants will peddle at ~25W at a minimum cadence of 60 rpm. Participants will wear a HR monitor during each session to ensure they are exercise at a safe, appropriate intensity. All HIIT sessions will be followed by a 5 min cool-down at ~25W.

During each whole body RE exercise session, participants will complete 2 upper body and 2 lower body exercises. Leg extension and leg press will be completed during every session, however the upper body exercises will alternate between chest press/horizontal row and shoulder press/biceps curl. For each exercise, participants will complete 3 sets of 8-12 repetitions at 80% 1RM, with the last set completed to failure. Each exercise session will be supervised by a member of the research team.

*6.5 Acute exercise protocol*

To assess the integrated MPS and acute satellite cell response to SUPP in the untrained and trained state, a set of 3 muscle biopsies (1 per day for 3 days) will be conducted at weeks 7 and 19. Immediately prior to participants’ first exercise session in week 7, a muscle biopsy will be taken (time-point: 0 hours). Biopsies will be taken again at 24 and 48 hours post-exercise. This process will be repeated ~1 week following participants’ last exercise session in week 19. Approximately ~ 8 mL of blood will be drawn from an antecubital vein after each biopsy is taken.

*6.6 Deuterated water protocol*

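### The planned group-by-time interaction and Tukey follow-up do not test the primary question, the between-arm difference in change during training (week 7 to week 19)

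*Protocol*

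**What the plan says.** Protocol section 2.0 puts the main question as "Primarily, whether the supplement is able to enhance exercise-mediated changes in muscle strength, physical function and body composition". Section 3.0 separates two ways in which benefit might arise: "Supplementation and exercise training will independently and synergistically increase muscle strength and physical function".

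The design in section 6.0 reflects that separation. "Phase 1 of the study is 6 weeks in duration and will be completed primarily at home", with beverages taken twice daily and no training: "Participants will be encouraged to maintain their normal diets and levels of physical activity". Training comes afterwards: "During Phase 2, participants will perform 3 exercise sessions per week for 12 weeks, while continuing to consume 2 study beverages per day". The full assessments are made before the study and then twice more: "These assessments will be repeated during week 7, and again upon completion of the study during week 19". Week 7 is thus the junction between supplement alone and supplement plus training. Strength (1RM) and VO2peak are also tested at weeks 11 and 15, to keep the training stimulus adequate.

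Section 9.0 applies one analysis to everything: "Data will be analyzed using a 2-way analysis of variance (ANOVA) with between (SUPP, PLB) and within (time) group comparisons". The follow-up is Tukey's "HSD post hoc testing will be used to assess differences between the means when interactions are detected". The section does not list the levels of time, and it does not say which result answers the primary objective.

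**The concern.** The question is about change during training, but the supplement starts six weeks before training does. An omnibus group-by-time interaction asks whether the arms' time courses differ anywhere, so a supplement effect complete by week 7 produces it as readily as one that appears during training. Hypothesis 1 expects the supplement to act independently of exercise, so the protocol itself anticipates some Phase 1 divergence.

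The follow-up does not close the gap. Tukey's HSD compares pairs of means, such as SUPP with PLB at week 19. A week-19 difference carried forward from week 7 looks the same as one gained through training. The quantity that matters, the difference between arms in the week 7-to-19 change, is never tested. At stake is the trial's main conclusion: a supplement-alone effect could be read as enhanced adaptation to exercise.

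**Working it through.** **Inputs from the protocol.** Section 5.0 gives 20 per arm after 20% dropout (20/0.80 = 25 recruited per arm), an effect of 1.75 to 3.25 kg, SD 1.5 kg and α = 0.05 (taken as two-sided). Section 6.1 gives three main visits.

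**Assumptions.** The protocol gives no within-person correlation ρ, so 0.5 to 0.9 is used with compound symmetry. It gives no Phase 1 effect either, so placing an effect in Phase 1 is an assumption.

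**The plan's own figure.** For 1.75 kg, SD 1.5 and 80% power, n = 2(1.960 + 0.842)² × 1.5²/1.75² = 11.5, so 12 per arm (13 with the t distribution). The stated 20 is not reproduced, but it errs on the safe side. The point here does not depend on it; 20 per arm serves only as the number of completers.

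**Omnibus interaction.** Let d be the between-arm difference once it has arisen and s the SD of change. The within-person error variance is s²/2, and the noncentrality is λ = (n/2) × Σ(dⱼ − d̄)² / (s²/2).

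- Phase 1-only effect: differences at pre, week 7 and week 19 are (0, d, d), so Σ = 2d²/3.
- Phase 2-only effect: differences are (0, 0, d), so Σ = 2d²/3 again.

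The two cases have the same λ, so the interaction test cannot tell them apart. With d = 0.91s, λ = 10 × (2/3) × 2 × 0.91² = 11.04. Against F(2, 76), critical value 3.12, this gives power 0.84. With d in units of s, ρ cancels. Simulation at ρ = 0.5, 0.75 and 0.9 agrees, at about 83-84%.

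If 1RM is analysed at all five visits, a Phase 1-only effect gives Σ = 4d²/5, λ = 13.25 and power 0.83 against F(4, 152).

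**Week 7-to-19 contrast.** This is a two-sample comparison of change on 38 df.

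- Phase 1-only: the true difference is zero, so it rejects in about 5%.
- Phase 2-only: noncentrality 0.91 × √(20/2) = 2.88, critical value 2.02, power 0.80.

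**In kilograms.** Reading 1.5 kg as the SD at one visit, s = 1.5√(2(1 − ρ)), which is 1.5 at ρ = 0.5 and 1.06 at ρ = 0.75. Interaction rates for a Phase 1-only effect, 20 per arm, three visits:

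| Phase 1 effect | ρ = 0.5 | ρ = 0.75 |
|---|---|---|
| 1.0 kg | 56% | 86% |
| 1.75 kg | 97% | over 99% |

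The contrast stays near 5% in every cell. If the 1.75 kg arises in Phase 2 instead, the contrast has about 94-95% power at ρ = 0.5 and over 99% at ρ = 0.75. With no effect in either phase, the omnibus test holds its 5% level.

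**Tukey step.** For 1.75 kg at ρ = 0.5, using a pooled cell error, SUPP and PLB differ significantly at week 19 in roughly three quarters of trials, whichever phase produced the effect. The week-7 comparison does discriminate: it is flagged in about 76-79% of trials for a Phase 1-only effect and under 1% for a Phase 2-only effect, across the correlations tried.

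**The case against.** Four points can be made for the plan.

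1. **The omnibus test is valid for what it tests.** It holds its level for any difference in time course, and hypothesis 1 makes a supplement-alone effect a hypothesised result. Detecting one is not in itself a false positive. This stands. A reader might infer that the sponsor will report any interaction as enhanced exercise adaptation, but section 9.0 does not say so. The fault is that no planned result answers the primary objective.

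2. **Time might mean weeks 7 and 19 only.** The interaction would then be exactly the contrast wanted. Nothing in section 9.0 says this, and the same outcomes are measured before the study, so all main assessments is the natural reading. The conclusion depends on it.

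3. **Tukey can locate the effect.** The week-7 comparison does give real, if indirect, help. It is less reliable with a within-person error term, where a Phase 2-only effect of 1.75 kg produces a false week-7 flag in about 4% of trials at ρ = 0.5 and roughly 35% at ρ = 0.9. In any case, setting significance at week 7 against significance at week 19 is not a test of the difference in changes.

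4. **Contrasts are often left to the SAP.** That would answer a complaint about missing detail. Here section 9.0 fixes both the test and its follow-up, and neither matches the objective.

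A reader might also infer that the Tukey step is itself badly anti-conservative or almost without power. The document does not support either claim. The error term is not stated, power varies widely with the correlation and the error term assumed, and Tukey runs only after a significant interaction. With that condition and a within-person error term, the null rate for a week-19 arm difference is only about 1-2.5%.

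**Conclusion.** The concern holds in this form: on the natural reading of time, neither step in section 9.0 tests whether SUPP enhances change during training. An effect of 0.91 SD of change gives an interaction in about 83-84% of trials whether it arises before or during training. The week 7-to-19 contrast separates the two cases, at about 5% against 80%.

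These rates assume 20 completers per arm, three visits and compound symmetry, and the Phase 1 effect is hypothetical. The equality of the two interaction rates does not depend on the size of the effect or on the correlation; it follows from the three-visit layout under compound symmetry.

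One limit applies to the contrast too. Both arms train in Phase 2, so it shows whether change during training differs between arms. It cannot separate synergy with exercise from a supplement effect that simply goes on accruing.

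**What to change.** In section 9.0, list the levels of time for each outcome. Name the SUPP minus PLB difference in change from week 7 to week 19 (one degree of freedom, from the repeated-measures model) as the test of the primary objective, to be made whether or not the omnibus interaction is significant. Name two secondary contrasts: pre-study to week 7 (supplement alone) and pre-study to week 19 (total effect). Tukey comparisons of means may stay, labelled exploratory.

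The cost is wording only, since every visit needed is already scheduled. The downside is that the all-pairs comparisons lose confirmatory standing.
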